#### Processing speed in schizophrenia

Recent meta-analyses have highlighted processing speed as being the central cognitive deficit in schizophrenia, with greater effect sizes than any other neurocognitive domain [62, 65]. Moreover, processing speed has been related to the deficit in emotion recognition in individuals with schizophrenia [66]. Specifically, processing speed is consistently shown to be a disproportionate deficit in schizophrenia against a backdrop of a generalized cognitive deficit [62, 67]. As such, it has been hypothesized that processing speed might mediate a broader array of cognitive impairments in schizophrenia [68]. Specifically, processing speed deficits have been shown to mediate impairments in attention, executive functions [68], verbal memory, verbal fluency, social cognition and functional outcomes [69]. While studies show that processing speed deficits can be partially explained by medication (for example, chlorpromazine) dosage, the evidence is also clear that processing speed deficits remain substantial even after accounting for medication effects [70]. In addition, impaired processing speed has been found in first-degree relatives of schizophrenia patients, as well as in individuals at high risk of developing the illness [62], suggesting that processing speed might be another biological marker of schizophrenia.

Importantly, processing speed correlates with numerous important clinical features in schizophrenia, including job tenure [71], self-care management, social functioning [72], and independent living [62]. Logically, increased response latency in social interactions likely hinders social relationships and social information processing. In addition, processing speed has been described as likely being the best longitudinal predictor of level of autonomy in patients with chronic schizophrenia [72]. Taken together, processing speed has a graded relationship with risk for schizophrenia, presence of schizophrenia, severity, and functional outcome, which supports the need for remediation efforts to address processing speed impairments.

### Processing speed training

#### Healthy individuals

Processing speed training has the primary aim of improving mental processing of increasingly complex information that can be processed accurately within briefer periods. The majority of the processing speed training literature in healthy populations focuses on older adults. For example, in a paper analyzing six different studies using a visual information processing speed-training paradigm, the authors found that speed of processing improved among 55 to 95 year olds, and that benefits of training lasted for at least 2 years in some cases [73]. In addition, improvements in processing speed were related to improvements in everyday functioning, including instrumental activities of daily living and driving abilities, providing evidence of far-transfer effects [73]. Importantly, one of the biggest predictors of cognitive gains following processing speed training is pre-training processing speed abilities, such that persons with slower initial speed benefit the most from training [73].

One recent study examined the effects of processing speed training in young, healthy adults [74]. This research group found that processing speed training (using several adaptive training tasks, such as a Visual Number Matching task) led to near-transfer improvements in processing speed in adults with a mean age of 21.6 years, although no evidence of far-transfer was found in measures of fluid intelligence, working memory, or inhibition [74]. Another group found increases in efficiency of attentional resource allocation, as measured by pupil dilation, following processing speed training in young adults [75]. Thus, there are mixed results on near- and far-transfer gains of processing speed training with healthy populations, with evidence suggesting that initial processing speed abilities are an important moderator in treatment outcomes.

Notably, some researchers have examined processing speed training as an active control condition in cognitive remediation studies (for example, compared to working memory training) [76], due to weak evidence of transfer effects, particularly far-transfer, associated with processing speed training in healthy adults [74]. However, a closer look at the literature suggests that individuals with lower initial processing speed (for example, older adults) can benefit from processing speed training, including both near-transfer effects and far-transfer effects (for example, improvements in activities of daily living) [73].

#### Schizophrenia patients

Given that schizophrenia patients have prominent deficits in processing speed and that processing speed has been strongly related to everyday functioning, it logically follows that processing speed training may be an important method of improving functioning in patients. Examinations of processing speed training with schizophrenia patients to date have solely been part of larger programs of cognitive remediation, with several studies finding that broad-based cognitive remediation programs lead to improvements in processing speed in patients [77–80]. Overall, a recent meta-analysis shows a medium-sized effect (*d* = .48) of general cognitive remediation therapy on improving processing speed across a total of 655 schizophrenia patients [4]. However, targeted processing speed training studies with schizophrenia patients are needed to better understand the mechanisms of processing speed enhancement through training in patients. Given that individuals with slower initial speed appear to benefit the most from training, coupled with the fact that schizophrenia patients typically have reduced processing speed abilities (that is, approximately 1 to 2 standard deviations below healthy controls) [81], the current study conceptualizes processing speed training as an active training condition rather than an active control condition for individuals with schizophrenia.

### Objectives and hypotheses

This study will investigate 1) near-transfer gains associated with working memory and processing speed training in schizophrenia patients (that is, gains in the working memory or processing speed domains, respectively); 2) far-transfer gains associated with working memory and processing speed training in schizophrenia patients (that is, gains in other neurocognitive domains, primarily fluid intelligence, and gains in social cognition); and 3) real-world gains associated with working memory and processing speed training in schizophrenia patients (that is, gains in daily functioning). In addition, exploratory analyses will examine the effect of individual difference variables (that is, sleep quality and intrinsic motivation) on training-related gains. The primary outcome measures are as follows: working memory, processing speed, and fluid intelligence.

The corresponding hypotheses are as follows: 1) post-training performance in working memory and processing speed will improve in the working memory training group and processing speed training group, respectively, relative to the no-training control group (that is, both training groups will show near transfer in their own domain); 2) both working memory and processing speed training will lead to more generalized improvements in other neurocognitive domains, particularly fluid intelligence, compared to the no-training control group, as well as enhancements in social cognition relative to the no-training control group; and 3) both working memory and processing speed training will lead to more improvements in daily functioning compared to the no-training control group. Given the current paucity of research comparing the gains associated with specific training programs, no hypotheses are made with regards to which training group (that is, working memory or processing speed) will show greater improvements in neurocognition, social cognition, or daily functioning. Rather, comparisons between training groups will be exploratory in nature.

## Methods/Design

### Study design

This study is a randomized controlled trial (RCT) and will be conducted at the Foothills Medical Centre and the University of Calgary in Calgary, Alberta, Canada. Participants who meet eligibility criteria will be randomly allocated to a working memory-training group, a processing speed-training group, or a no-training control group. The study will employ a parallel design with a 1:1:1 allocation ratio. Participants allocated to the working memory-training group or processing speed-training group will directly receive the specified cognitive training intervention, whereas those allocated to the no-training control group will be given the opportunity to receive one of the two cognitive training interventions after a waiting period of 10 weeks. Assessments are planned both before and after the intervention for the experimental groups, and both before and after the 10-week wait period for the control group.

### Recruitment process and study population

Up to 81 schizophrenia patients will be recruited. This is based on a power calculation with an alpha-level of .05, power of .80, and an effect size of *d* = .70, with the effect size derived from a recent study examining a more specific cognitive remediation program (that is, auditory working memory training) in schizophrenia [58]. Importantly, this sample size accounts for dropout rates of up to 10 %, based on previous cognitive training studies [82]. Recruitment status is currently pending, with plans to start in January 2016. Patients will be recruited through outpatient clinics at Foothills Medical Centre and through community support programs in Calgary, Alberta, after receiving appropriate permissions to enter the clinics and discuss the study. Participants will also be recruited through an existing participant database at the University of Calgary. Inclusion criteria for all participants will be as follows: (1) a diagnosis of schizophrenia or schizoaffective disorder, assessed with the Structured Clinical Interview for DSM-5 (SCID-5) interview; (2) age 18 to 65 years; (3) no uncorrected visual impairment, including color blindness, determined by self-report; (4) no uncorrected hearing impairment, determined by self-report; and (5) able to provide informed consent, determined by the clinical experience of the researchers. Exclusion criteria will be as follows: (1) meeting Diagnostic and Statistical Manual - 5^th^ edition (DSM-5) diagnostic criteria for a current major depressive episode, manic episode, or hypomanic episode, assessed with the SCID-5 interview; (2) use of electroconvulsive therapy (ECT) or transcranial magnetic stimulation therapy (TMS) within the past month, determined by self-report; (3) recent (that is, within past 3 months) history of substance-use disorder (excluding nicotine, cannabis, or caffeine), assessed with the SCID-5 interview; (4) diagnosed with a medical condition known to affect cognition (for example, endocrine disease or uncontrolled diabetes), determined by self-report; and (5) score less than 70 on the Wechsler Abbreviated Scale of Intelligence (WASI-II). In addition, only individuals who have access to the internet on a home computer will be eligible to participate in the study.

See Fig. 1 for participant flow chart. Participants who are interested will sign a “consent to contact” form and will be contacted by the research team via e-mail and/or telephone, or participants can contact the study investigators themselves through the provided e-mail and/or telephone number. Interested participants will undergo a telephone screening process to ensure that they meet the aforementioned inclusion criteria. Those who meet eligibility criteria will be invited for the first baseline assessment (see full battery below), which will include confirming clinical diagnoses with the SCID-5 Research Version. Participants whose schizophrenia or schizoaffective disorder diagnosis is confirmed with the SCID-5 will be invited for the second baseline assessment, which will include pre-training cognitive assessment (see full battery below). Participants will be instructed to continue taking their medication throughout study participation, and information regarding medication usage and dosage will be collected at pre- and post-assessments.

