### Cognitive remediation in schizophrenia

Given the array of cognitive deficits associated with schizophrenia and their relation to daily functioning, numerous research groups have examined the impact of cognitive remediation on many aspects of cognition (for example, attention, memory, executive functions, social cognition, and fluid intelligence). At the 2010 Cognitive Remediation Experts Workshop, cognitive remediation was described as a behavioral-training intervention with the aim of improving cognitive abilities and a specific emphasis on both generalizability and durability [18]. Several reviews and meta-analyses have been published on the benefits of cognitive remediation in schizophrenia patients [4, 5]. Results from these meta-analyses typically indicate promising results from cognitive remediation programs. For example, one meta-analysis examining 26 studies (1,151 subjects) found significant effect sizes for overall cognition, as well as most individual domains of cognitive functioning, including effect sizes of *d* = .41 in global cognition, *d* = .41 in attention, *d* = .48 in processing speed, *d* = .52 in verbal working memory, and *d* = .47 in reasoning/problem solving [4]. Similar effect sizes were found in a more recent meta-analysis examining the effects of cognitive remediation (for example, effect size of *d* = .45 in global cognition) [5].

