#### Individuals with schizophrenia

Relatively few studies have examined the effects of working memory training on individuals with schizophrenia; however, studies that have been completed do show promising results. For example, one research group reported improvements in visual working memory, verbal working memory, and visual short-term memory in chronic schizophrenia patients following just 4 weeks of computerized working memory training (that is, verbal and visuospatial working memory tasks), compared to a control group without intervention [57]. In another study, a computerized training program aimed at improving lower-level auditory processing (for example, distinguishing between sound frequencies, phonemes, and syllables) in addition to auditory-verbal working memory and verbal learning (for example, remembering verbal instructions and details from conversations) was compared to a control computer game program with schizophrenia patients [58]. The results of this study showed that individuals with schizophrenia receiving the active training program, as compared to the control program, had significant gains in verbal working memory, verbal learning and memory, as well as global cognition after 10 weeks of training [58]. Notably, the effect sizes found in this auditory working memory-training study were greater than the majority of studies reported in a recent meta-analysis by McGurk and colleagues [4] on cognitive remediation in schizophrenia patients. Given that the studies reported in the meta-analysis were typically broad-based examinations of cognitive remediation involving multiple domains, it may be the case that targeted working memory training is more effective at improving both working memory abilities, as well as general cognition [4, 58].

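### For the planned training-versus-control comparison of gains, 81 patients do not give 80% power at d = .70 once 10% dropout is allowed for

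*Protocol article*

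**What the plan says.** The sample-size statement is in the Protocol article, Recruitment process and study population. It opens with "Up to 81 schizophrenia patients will be recruited" and continues: "This is based on a power calculation with an alpha-level of .05, power of .80, and an effect size of" d = .70, a value taken from one study of auditory working memory training. It then says that "this sample size accounts for dropout rates of up to 10" per cent.

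Under Study design, "The study will employ a parallel design with a 1:1:1 allocation ratio", and the randomisation text puts 27 participants in each arm.

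The comparison to be powered follows from two other sections. Objectives and hypotheses frames each hypothesis as a training group against the no-training control; the two training groups are not pooled, and comparisons between them are exploratory. Statistical analysis first lists a three-group by two-time repeated measures ANOVA. It then plans independent t-tests of training-related gains for each training group against control, tied to the a priori objectives, with Cohen's d reported.

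The article does not state sidedness, the test behind the calculation, the SD by which d is standardised, or a pre-post correlation.

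**The concern.** The article prints alpha, power, effect size, dropout and total, so the figures can be checked against each other. A standardised difference of .70 between two arms, tested two-sided at .05, needs clearly more than 27 per arm, and more again after dropout. The total looks too small for the comparison that the hypotheses name.

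What is at stake is how the results are read. With a claimed power of .80, a non-significant training-versus-control gain suggests that an effect of the assumed size would probably have been seen. If the real figure is about two in three, that inference is weaker than readers would take it to be, for near transfer and for fluid intelligence alike.

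**Working it through.** **Inputs from the article.** Total 81; three equal arms, so n = 27 enrolled per arm; 10% dropout leaves 27 × 0.9 = 24.3, about 24 completers per arm; d = .70; alpha .05; target power .80.

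**Assumptions, because the article is silent.** Two-sided test (one-sided also shown); d in units of the gain-score SD, the variable the t-test uses.

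**Step 1. Try to reproduce 81 with the planned t-test.**

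Normal approximation: n per arm = 2(z₁₋α/₂ + z₁₋β)²/d² = 2(1.960 + 0.842)²/0.49 ≈ 32.04, so 33. The exact noncentral-t calculation gives 34.

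- Two-sided: 34 × 3 = 102 evaluable. With dropout, 34/0.9 = 37.8, so 38 per arm, or 114.
- One-sided: 26 × 3 = 78 evaluable. With dropout, 26/0.9 = 28.9, so 29 per arm, or 87.

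Neither gives 81 with dropout included.

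**Step 2. Power at the planned size.** Noncentrality = d√(n/2), with 2n − 2 degrees of freedom.

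| Per arm | Noncentrality | Two-sided power | One-sided power |
|---|---|---|---|
| 27 (no dropout) | .70 × √13.5 = 2.57 | .714 | .814 |
| 24 (10% dropout) | .70 × √12 = 2.42 | .661 | .772 |

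The detectable d at 80% power, two-sided, is .83 with 24 per arm and .78 with 27.

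**Step 3. Other calculations that might lie behind 81.**

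- *One-way F test on gains.* If both training arms exceed control by .70, f = .70 × √2/3 = .33. That needs 93 in equal arms before dropout; power is .74 at 81 and .69 at 72. With f = d/2 = .35, power is .80 at 81 and .74 at 72, so the target is met only if nobody drops out.
- *Both training arms pooled against control, 48 versus 24, two-sided.* Power .79. This is close to target, but it is not the stated hypothesis.
- *Between-groups factor of a repeated-measures ANOVA, two time points, f = .33, assumed correlation r = .5.* Noncentrality = N f² × 2/(1 + r). At N = 72 this is 72 × .1089 × 1.333 = 10.45, and power passes .80 (70 is enough if equal arms are not required). Then 72/0.9 = 80, and the next multiple of three is 81. This lands on the printed total. It tests the average of the pre and post scores across groups, though, not the group-by-time interaction or the gain.

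**Step 4. If d = .70 is in raw-score SD units.** Power then depends on the pre-post correlation r. At 24 per arm, 80% needs an effective d of .826.

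- Change scores: d/√(2(1 − r)) = .826 gives r = 1 − (.70/.826)²/2 ≈ .64.
- Baseline-adjusted ANCOVA: d/√(1 − r²) = .826 gives r = √(1 − (.70/.826)²) ≈ .53.

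For change scores, power at 24 per arm is .52 at r = .3, .66 at r = .5, .76 at r = .6 and .86 at r = .7.

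**The case against.** The strongest reply has four parts.

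*The total can be reproduced.* The repeated-measures between-groups calculation gives 80 with dropout, or 81 in equal arms. This stands as an explanation of where 81 may have come from, and a reader who inferred that no standard calculation gives 81 would be wrong. It does not rescue the claim. It relies on an assumed r of .5 that the article does not state, and it averages over time while the hypotheses concern gains.

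*The 66% rests on choices the article does not make.* Sidedness is unstated and the hypotheses are directional; the t-tests are called follow-up tests; d could be in raw-score units. This stands in part, so 66% has to be quoted with its conditions. A one-sided test still falls about three points short after dropout. The t-tests are the tests tied to the a priori objectives. The raw-score reading reaches 80% only at a correlation of about .64 or more.

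*A condensed article may leave such details to a fuller document.* True, and their absence is not the point. The point is that the printed power and dropout cover are not met by the planned comparison unless something further is assumed.

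*The choice of d = .70.* A reader might infer that this value is itself an error. The article says that "the effect sizes found in this auditory working memory-training study were greater than the majority of studies reported in a recent meta-analysis", and the meta-analysis it cites gives d = .48 for processing speed and .52 for verbal working memory. But the article also gives its reason: the source study trained a specific domain, while the pooled studies were mostly broad-based. That is a disclosed and argued planning judgement, so it forms no part of the error.

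**Conclusion.** The point holds for the comparison that the protocol's hypotheses and analysis section name. With d in gain-score SD units, 81 patients with 10% dropout give power of about .66 two-sided or .77 one-sided, against the stated .80. Two-sided, the target is missed even with no dropout (.71). One-sided, it is met only when almost nobody drops out, which contradicts the dropout statement.

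The documents do not support saying that the trial's power simply is 66%. If d is in raw-score units and the pre-post correlation is high enough, 80% is attainable; the article gives no correlation from which to judge.

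**What to change.** Keep 81 and do one of two things in the sample-size paragraph.

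1. Restate the figures for the training-versus-control comparison of gains: about 24 completers per arm, two-sided alpha .05, power about .66 at d = .70, detectable d about .83. Withdraw the statement that 80% power survives 10% dropout.
2. If d = .70 is in raw-score SD units, say so, and state the sidedness, the analysis and the assumed pre-post correlation. For 80% two-sided at 24 per arm this must be at least about .64 for change scores or about .53 for ANCOVA. If ANCOVA is relied on, the analysis section must name it, since it currently plans repeated measures ANOVA and t-tests on gains.

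Power at the article's own meta-analytic values may be added as a sensitivity figure: with 24 per arm, two-sided and in gain-score SD units, .37 at d = .48 and .42 at d = .52.

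The cost of the first option is a reworded paragraph and a less favourable stated power. The second also needs a justified correlation. Neither adds patients, and recruitment had not started when the article was written.

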**Fig. 1 Fig1:**
[figure not shown]
Participant flow through study. This figure illustrates participant enrollment, allocation, and follow-up throughout the study

All participants who meet the inclusion criteria will be randomly assigned to one of three conditions: (1) a working memory-training condition (27 participants), (2) a processing speed-training condition (27 participants), or (3) a no-training control condition (27 participants). Participants in the two training conditions will be blind to the fact that there are multiple training groups and to which cognitive domain they have been assigned to (that is, no mention of “working memory” or “processing speed” will be made). Group assignment will be determined by a Microsoft Excel randomization generator (that is, computer-generated random numbers). The random allocation sequence will be generated by a trained research assistant. Randomization will be performed as complete randomization with a 1:1:1 allocation. The allocation sequence will be concealed in sealed envelopes until the end of the pre-training assessment. A trained research assistant will also assign participants to interventions. Participants who are randomly assigned to the no training control condition will be given the opportunity to access the cognitive training games after their post-assessments. All researchers administering pre- and post-assessments will be blind to the group assignments of each participant.

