### Data sets analyzed

All eligible participants who are randomized into the study and complete at least 50 % of the cognitive training will be included in the completer analysis, following similar cut-offs in prior cognitive training research [Lawlor-Savage L, Goghari VM: Dual n-back working memory training in healthy adults: a randomized comparison to processing speed training, submitted]. All eligible participants who are randomized into the study will be included in the intent-to-treat analysis. Data collection will stop when the goal sample size has been reached or when new participants are unable to be recruited for a significant period.

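### Complete randomization, as named, does not deliver the stated 27 patients per arm; the cost is a small loss of precision, and a permuted-block list would remove it

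*Protocol article*

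**What the plan says.** All of this is in the protocol article.

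- **Total.** Recruitment process and study population: "Up to 81 schizophrenia patients will be recruited". The justification there is alpha .05, power .80, d = .70 and dropout of up to 10%.
- **Arm sizes.** The text below Fig. 1 in the same section fixes all three: "a working memory-training condition (27 participants"), "a processing speed-training condition (27 participants") and "a no-training control condition (27 participants").
- **Method.** The same paragraph continues: "Group assignment will be determined by a Microsoft Excel randomization generator (that is, computer-generated random numbers"), and then "Randomization will be performed as complete randomization with a 1:1:1 allocation".
- **Concealment.** "The allocation sequence will be concealed in sealed envelopes until the end of the pre-training assessment". Numbering of the envelopes is not mentioned.
- **Stopping of recruitment.** Data sets analyzed: "Data collection will stop when the goal sample size has been reached or when new participants are unable to be recruited" for a significant period.
- **Use of the control arm.** Statistical analysis compares each training arm with the same no-training arm by independent t-tests.

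**The concern.** A fixed count per arm and an unrestricted method of allocation stand side by side, and the second does not produce the first. Complete randomization normally means that each assignment is independent of those before it, so arm sizes vary by chance.

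The control arm matters most. All three hypotheses under Objectives and hypotheses set a training arm against the no-training group, so a small control arm weakens every planned contrast at once. Patients cannot be moved between arms afterwards. Nor does the method keep the arms in step over time, although patients come from outpatient clinics, community programs and an existing database. This is not a detail left to a fuller document: the article names the method.

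**Working it through.** **Inputs from the protocol article:** total 81; 27 per arm; 1:1:1; alpha .05; power .80; d = .70; dropout up to 10%. **Assumption:** two-sided tests, because sidedness is not stated.

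**1. The plan's own figure.** For a two-sample t-test the noncentrality is 0.70/√(1/n₁ + 1/n₂).
- With 27 v 27 it is 0.70/√(2/27) = 2.57 on 52 df, giving two-sided power .714 before dropout. The stated .80 is not reproduced.
- Two-sided .80 needs 34 per arm; 34/0.9 rounds up to 38, or 114 in total.
- One-sided .80 needs 26 per arm; 26/0.9 rounds up to 29, or 87 in total.

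This gap is a separate matter. Here .714 serves only as the equal-arms reference.

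**2. Chance of the stated arm sizes under independent draws.**
- P(27/27/27) = 81!/(27!³ × 3⁸¹) = .0101.

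**3. Spread of arm sizes under independent draws.**
- The control arm is Binomial(81, 1/3), with mean 27 and SD √(81 × 1/3 × 2/3) = √18 = 4.24. Its central 95% range is 19 to 35.
- P(control ≤ 22) = .144; P(control ≤ 20) = .060.
- By simulation (400,000 draws), the mean smallest arm is about 22.7. Some arm is 5 or more away from 27 in 54% of draws, and largest minus smallest is 10 or more in 40%.

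**4. What this does to power** (two-sided, d = .70, before dropout, noncentral t).

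| Control v training arm | Noncentrality | Power |
|---|---|---|
| 27 v 27 | 2.57 | .714 |
| 22 v 29.5 (other 59 shared equally) | 2.48 | .683 |
| 20 v 30.5 (other 61 shared equally) | 2.43 | .664 |
| Average over all multinomial splits of 81 | – | .704 |

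The average loss is .714 − .704 = .010. It is .031 with a control arm of 22 and .050 with one of 20.

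**5. The other reading: a shuffled list of 27+27+27 labels.** Counts are exact at 81, so steps 2 to 4 do not apply. As an illustration (60 is assumed, not in the document), stop such a list at 60 patients. The arms then differ by 5 or more in a little over a third of draws. Average power is .575 against .578 for 20/20/20, so imbalance costs about 0.3 points. The rest of the fall is due to the smaller total.

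**6. Check of the remedy.** Blocks of 3, 6 and 9 in random order, simply cut at 81, give exactly 27/27/27 in about two thirds of 50,000 simulated lists, with arms at most 3 apart otherwise. Lists built from whole blocks that total 81 give 27/27/27 every time.

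**The case against.** The strongest reply is that unrestricted is an interpretation. A paragraph that lists 27, 27 and 27, then a 1:1:1 ratio, then a prepared sequence in envelopes, could describe a shuffled list of 81 labels. That reading is possible and, if it is right, the 1% figure falls away. It does not settle the matter: the article does not say so, the term it uses ordinarily means independent draws, and recruitment may end below 81. The ambiguity therefore stands as a defect, though a less costly one.

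The second reply is that independent draws are a legitimate method. They are fully unpredictable, and the planned t-tests and group-by-time ANOVA can be run with unequal arms. This is also true. A reader might infer from the 1% figure that the comparison would be biased or invalid. The documents do not support that, because chance inequality of arm sizes does not bias a randomized comparison.

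A reader might also infer a 5-point loss of power when the control arm falls to 22, from .714 to .665. That figure keeps the training arm at 27. With 81 randomized, the five missing controls are in the training arms, and the loss is about 3 points.

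The remark about several recruitment sources stays qualitative: no drift over time can be quantified from the document, and Statistical analysis provides for correcting baseline differences.

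**Conclusion.** The point holds at modest size. The method as named does not guarantee the arm sizes stated beside it. Under independent draws 27/27/27 occurs about 1% of the time, the smallest arm is expected to be about 22.7, and the shared control arm has a 14% chance of 22 or fewer. The price is about 1 point of power on average, about 3 points with a control arm of 22 and about 5 with one of 20. These figures assume 81 randomized, two-sided .05, d = .70 and no dropout. Under the shuffled-list reading only an early stop leaves the arms unequal, and the cost is a fraction of a point.

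It would be wrong to conclude that balanced allocation restores the planned power: equal arms of 27 still give about .71 two-sided before dropout. The change is worth making because it is cheap and brings method and stated counts into agreement.

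**What to change.** Before the first patient:

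- Replace complete randomization with a computer-generated permuted-block list. Block sizes should be multiples of 3 (for example 3, 6 and 9), vary at random, and be constrained to total 81. This gives 27 per arm at full recruitment. If recruitment ends early, the arms are at most 3 apart with blocks of up to 9.
- Have the list prepared by someone who does not enrol, assign or assess, and keep the block sizes from those who do. The article gives both sequence generation and assignment to a trained research assistant without saying whether these are different people.
- Keep the sealed envelopes and add sequential numbering.

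If a shuffled list of 81 labels was intended, the text should at least say so; blocking would still protect against an early stop.

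The cost is one new list and a short change of text. Recruitment had not begun according to Trial status. The drawback is slight predictability at the end of a block, since the last assignment in a known block of 3 is determined. Varying, hidden block sizes limit this, as does opening each envelope only after the pre-training assessment.
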